## Abstract

**Background:**

Depression is a debilitating and costly disease for our society, especially in the case of treatment-resistant depression (TRD). Repetitive transcranial magnetic stimulation (rTMS) is an effective adjuvant therapy in treatment-resistant unipolar and non-psychotic depression. It can be applied according to two therapeutic strategies after an initial rTMS cure: a further rTMS cure can be performed at the first sign of relapse or recurrence, or systematic maintenance rTMS (M-rTMS) can be proposed. TMS adjuvant to treatment as usual (TAU) could improve long-term prognosis. However, no controlled study has yet compared the cost-effectiveness of these two additional rTMS therapeutic strategies versus TAU alone.

**Methods/design:**

This paper focuses on the design of a health-economic, prospective, randomized, double-blind, multicenter study with three parallel arms carried out in France. This study assesses the cost-effectiveness of the adjunctive and maintenance low frequency rTMS on the right dorsolateral prefrontal cortex versus TAU alone. A total of 318 patients suffering from a current TRD will be enrolled. The primary endpoint is to investigate the incremental cost-effectiveness ratio (ICER) (ratio costs / quality-adjusted life-years [QALY] measured by the Euroqol Five Dimension Questionnaire) over 12 months in a population of patients assigned to one of three arms: systematic M-rTMS for responders (arm A); additional new rTMS cure in case of mood deterioration among responders (arm B); and a placebo arm (arm C) in which responders are allocated in two subgroups: sham systematic M-rTMS and supplementary rTMS course in case of mood deterioration. ICER and QALYs will be compared between arm A or B versus arm C. The secondary endpoints in each three arms will be: ICER at 24 months; the cost-utility ratio analysis at 12 and 24 months; 5-year budget impact analysis; and prognosis factors of rTMS. The following criteria will be compared between arm A or B and arm C: rates of responders; remission and disease-free survival; clinical evolution; tolerance; observance; treatment modifications; hospitalization; suicide attempts; work stoppage; marital / professional statues; and quality of life at 12 and 24 months.

**Discussion:**

The purpose of our study is to check the cost-effectiveness of rTMS and we will discuss its economic impact over time. In the case of significant decrease in the depression costs and expenditures associated with a good long-term prognosis (sustained response and remission) and tolerance, rTMS could be considered as an efficient treatment within the armamentarium for resistant unipolar depression.

**Trial registration:**

ClinicalTrials.gov, NCT03701724. Registered on 10 October 2018. Protocol Amendment Version 2.0 accepted on 29 June 2019.

## Background

Depression is a debilitating difficult-to-treat disease associated with enormous costs for our society. According to the Global Burden Study in 2010, it is a leading cause of morbidity and disability worldwide, thus a public-health priority calling for cost-effective interventions [1]. Affecting the whole lives 24% of French people [2], the direct and indirect yearly cost for depression is estimated at 14 billion Euros in France [3]. These expenditures include co-morbidities such as substance abuse, suicide attempts and suicide achieved, somatic multi-morbidities, loss of production, working stoppages, the increased use of the healthcare system (hospitalization, etc.), the impact on the quality of life and its socio-professional aftermath [3–5]. Despite appropriate treatment, 40% of patients do not respond to initial antidepressant treatment and 20% present with a chronic form of depression (> 2 years despite standard treatment administered correctly) [6]. Typically, treatment-resistant depression (TRD) refers to an absence of remission after at least two different antidepressant lines at an effective dosage over a period of 6 weeks during the current episode. Indeed, 30%–40% of patients with major depression hold disabling symptoms after several antidepressant treatments [7–9]. Even in the cases of initial remission, the study of reference for pharmacotherapy, STAR*D, shows a 43% rate of relapse at 1 year [7, 10]. The economic cost of depression is much higher in the case of TRD [11, 12] and is associated to the higher rate of medication non-observance at around 63% [5]. Depression after two antidepressant agents increases the cost of care by 40%–100% in comparison with non-TRD [13]. Moreover, in 2000, a meta-analysis of Dimatteo et al. [14] demonstrated that the non-observance rate of non-psychiatric treatments is three time higher among patients with anxio-depressive syndrome increasing its global burden. Care for depression is therefore a challenge with important direct and indirect costs in the short and long term, especially in its treatment-resistant form.

The gold-standard treatment of TRD is still electroconvulsive therapy (ECT), especially for depression with psychotic symptoms, severe resistance to pharmacological therapies, or life-threatening episodes, with a 48% response rate in ultra-resistant episodes [5, 15]. Repetitive transcranial magnetic stimulation (rTMS) is a non-invasive, focal and cortical stimulation technique enhancing neuronal plasticity throughout the modulation of cortical excitability [16]. This technique is an interesting alternative to ECT for resistant and middle to severe unipolar depression without psychotic symptoms [17], especially in conjunction with antidepressant chemotherapy [18, 19]. Two types of stimulations are widely applied – high frequency on the left dorsolateral prefrontal cortex (DLPFC) and low frequency on the right DLPFC – with evidence suggesting similar efficacy [20], and with the advantage for the 1 Hz protocol to be faster and better tolerated [21]. Since 2008, high frequency rTMS on the left DLPFC is validated in the United States by the Food and Drug Administration (FDA) to treat unipolar depression after the failure of one antidepressant treatment based on the study by O’Rearden et al. [22] involving 301 participants. Similar efficacy was shown among 170 patients with unipolar depression in France using low frequency rTMS on the right DLPFC [23]. In international guidelines, rTMS in the acute phase reached the best level of evidence (level 1) [17] after failure of one antidepressant. rTMS has the advantage of being somatic and cognitively well tolerated [24], without drug interaction [25], and improving the quality of life [26] with a huge rate of observance (an average rate of 3% for dropouts) [21].

However, the rates of relapse and recurrence at 6-month follow-up may be comparable to the ECT [27]. These rates are in the range of 60% without consolidation to 30% with consolidation (pharmacological therapies or consolidation ECT) [28]. Having these comments, two therapeutic strategies are possible: a further rTMS cure can be performed at the first sign of relapse or recurrence [29], especially for patients with a good previous response [30]; or systematic maintenance rTMS (M-rTMS) can be carried out in the immediate future [31]. It is, therefore, essential to evaluate the cost-effectiveness of these alternatives treatment for TRD. It is already established that rTMS is more cost-effective (efficiency) than placebo [32] and rTMS is more efficient than a third-line antidepressant treatment in an Australian context [33]. But no controlled study compared in the long term (12 months) the cost-effectiveness of these two rTMS therapeutic strategies versus treatment as usual (TAU) alone (any therapeutic strategy agreed to by patients and psychiatrists including medication, ECT, and psychotherapy). Our main hypothesis is that additional M-rTMS will be more cost-effective at 1 year than TAU alone.

### Specific aims

The aim of this health-economic study is to investigate the incremental cost-effectiveness ratio (ICER) (ratio costs / quality-adjusted life-years [QALY]) of the curative and maintenance rTMS versus TAU over 12 months in a population of patients suffering from unipolar TRD (Montgomery and Asberg Rating Scale [MADRS] score of ≥ 20). QALY evaluation is measured by the Euroqol Five Dimension Questionnaire (EQ-5D). Moreover, this trial evaluates the budget impact of the most efficient strategy at 5 years, prognosis factors of successful maintenance after rTMS response to a cure, the cost–utility ratio (costs / QALY), and the cost-effectiveness analysis (life years gains [LYG]) (costs/LYG) at 24 months.

## Methods/design

### Study design, setting, and recruitment

This is a health-economic, prospective, randomized, double-blind, multicenter, parallel-arm study funded by the French Ministry of Health (Reference: 030/2018). The sponsor is the Centre Hospitalier Universitaire (University Hospital) of Nantes, France. The patients are randomly assigned to (Fig. 1):
▪ Arm A with active rTMS cure and systematic maintenance M-rTMS for responders (> 50% decrease in MADRS total score);▪ Arm B with a new course of active rTMS at the first sign of depression relapse or recurrence for responders;▪ Arm C with sham cure. In this arm, 50% of responders have systematic placebo rTMS maintenance after the cure (arm C1) and the other 50% have placebo rTMS cure at the first sign of depressive relapse or recurrence (arm C2).

**Fig. 1 Fig1:**
[figure not shown]
Flow chart

The other standard cares will be conducted as usual in accordance with clinical practices, guidelines, psychiatrists, and patient preferences throughout the study. In the three arms, the non-responders will receive TAU including pharmacotherapy, psychotherapy, and ECT if needed. Moreover, the evaluation of healthcare resources consumed by patients are investigated during the follow-up. The main endpoint is at 12 months, and 24 months for secondary outcome measures. After the 12-month follow-up, the center is free to choose medical care as they wish according to their usual practices (e.g. TAU or rTMS course as needed).

The present study has been approved by the Ethics Committee (reference: 030/2018, RCB no. 2018-A00473–52, last amendment version 2.0 accepted 29 June 2019) and compiled in accordance with the principles of the Declaration of Helsinki (final version 2004) as well as French legislation (article L1121–160 and L1126–7 of the Public Health Code). Participants give their oral consent to take part in the study. Written and verbal information about the study aim and procedures is provided to all the volunteer participants. Investigating physicians will obtain informed consent or assent from potential trial participants. This consent will be traceable in the medical record as recommended by the ethical committee and the French legislation for interventional studies with minimal risk. Information form and consent modalities are available from the corresponding author on request. Participants are asked if they agree to the use of their data should they choose to withdraw from the trial. Participants will also be asked for permission for the research team to share relevant data with people from the University taking part in the research or from regulatory authorities, where relevant. The aim is to enroll 318 patients who have been put forward either by private or hospital psychiatrists, previously informed in writing of the study. There is no anticipated harm or compensation for trial and post-trial participation; this trial does not involve collecting biological specimens for storage.

### Inclusion criteria

The 318 patients aged ≥18 years must present with a current depressive episode with duration between 12 weeks and 3 years considered major according the Diagnostic and Statistical Manual of Mental Disorders, 5th edition (DSM-5) [34], with a MADRS score of ≥ 20 [35] and treatment-resistant with an absence of remission after at least two different antidepressants lines at an effective dosage over a period of 6 weeks during the current episode. TRD includes resistance to antidepressants and validated potentialization agents as quetiapine or lithium [36]. The current treatment may have to be stable for 6 weeks before the baseline and to be continued at a stable dose throughout initial rTMS course. Each individual must be able to: understand the information; take a decision; volunteer to participate; complete the required questionnaire; take orally administrated treatment independently or have the adequate assistance to do so throughout the study; and go to the research center for successive follow-up visits.

### Non-inclusion criteria

Patients presenting with at least one of the following criteria are not enrolled in the study: diagnostic of a depression with psychotic symptoms; current depressive episode better explained by an organic affection or a pharmacological treatment (corticosteroids, interferon, etc.); schizophrenia or psychotic disorder; bipolar disorder; neurologic disease including epilepsy, neurosurgical affection, and significant neurodegenerative disease; intellectual deficiency; a failure of rTMS cure during the current depressive episode, or a personal history of rTMS cure failure, with a protocol using 1 Hz rTMS on the right DLFPC with a minimum of 20 sessions per cure; a failure of ECT cure during the current depressive episode, or a personal history of ECT failure, including a minimum of 12 sessions per cure; history of previous maintenance ECT or at least two course of ECT; contraindication to the practice of rTMS (history of epilepsy or unexplained seizures, neurologic condition such as stroke, trauma, infection, tumor, severe migraine, any ferromagnetic material or implanted device using physiological signals); minors or persons deprived of liberty following a legal or administrative decision or hospitalized without consent, in guardianship; and pregnant and nursing women or women of child-bearing ge who are not using contraception. The same applies for individuals unable to agree with longitudinal follow-up.

### Study process

The screening visit V1 includes the Patient Information Leaflet, collection of the Consent Form and checking of inclusion and exclusion criteria. The medical research teams will be in charge of enrollment and assignation of participants to the intervention. A clinical examination is also carried out and a magnetic resonance imaging (MRI) scan performed in case of neuronavigation use.

### Randomization

During the baseline inclusion visit, the inclusion and exclusion criteria are checked and participants randomized by center into three groups by a computerized random number generator with a permuted block design without stratification or minimization. Participants are randomized to one of the treatment arm using a computer program included in the electronic case report form (eCRF). Initial randomization is performed according the ratio 1:1:0.5:0.5, respectively, corresponding to arm A, arm B, arm C1 (systemic sham rTMS maintenance for responders), and arm C2 (sham rTMS maintenance at the first sign of depressive relapse or recurrence for responders). Block size and type of variation (fixed or randomly) are not known by the investigators to maintain adequate blinding. Randomization occurs in a recorded delay of maximum 15 days before first rTMS or placebo session.

### Blinding

Masking is triple and includes participants, outcome assessors, and investigators. The sham stimulation applied with an identical rTMS procedure at the same location using a commercial figure-eight sham coil. However, it does not produce the same tactile sensation. A local electrical stimulation is delivered with two electromyogram electrodes using a transcutaneous electrical nerve stimulation (TENS) stimulator. At 1 year, patients will be asked to know which treatment (active or placebo) they think they had to evaluate the placebo quality. Just after the randomization, an automatic email with the allocated sequence will be sent to the research nurses who perform the rTMS session in their individual professional mailbox. Investigator and clinical research assessors will be informed of the rTMS schedule (systematical M-TMS or novel rTMS cure) but not the active or sham nature of the treatment.

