### Statistical analysis

Descriptive analysis of the data collected during each patient evaluation will be carried up until the final evaluation. Specific time points for analysis in the three groups are: baseline; at 1 month after the last rTMS or sham sessions; and 12 and 24 months after the end of the first rTMS or sham course. Continuous variables will be described using median, standard deviation, minimal, maximal, and range for quantitative variables; qualitative variables will be described using frequencies and percentages. No data about quality of life, healthcare consumed, and the cost are available in the literature for this indication, making a priori the calculation of number of individuals needed impossible. The number of participants required for the present study was calculated according to the expected and sustained response in each arm (> 50% decrease in MADRS total score). This rate of responder after the rTMS cure is estimated at 60% in arms A and B at 1 year with 50% of success of rTMS [23, 48]. According to the literature, we hypothesized a rate of 30% maintained response at 1 year for arm A [23, 31, 49, 50] and arm B [23, 50–52], and 11% for arm C [53]. Assuming a 5% (bilateral) type I error, a power of 80%, and an attrition rate of 80%, a total of 318 individuals is required (106 in each arm). The study includes three arms, but only two comparisons will be carried out: arm A versus arm C, and arm B versus arm C.

For the ICER, resources consumed, including costs and QALY, will be presented with average and dispersion for each group. The comparison between cost, QALY, and the years of life gained in each arm, including ICER analysis, will be evaluated with the estimation of their standard deviation and their corresponding 95% confidence intervals (CI) following the non-parametric bootstrap method [54]. Tables will present differences between the three groups including their costs, QALY, and ICER. The ICER is calculated to consider the possibilities of vast dominance between these strategies [55]. For example, the ICER between arms A and C will be calculated as follows:

$$ ICER=\frac{C_{armA}-{C}_{armC}}{QALYs_{armA}-{QALYs}_{armC}} $$

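### Outcome assessors are called masked but are told the rTMS schedule, which is unbalanced between each active arm and pooled arm C

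*Protocol article*

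**What the plan says.** All references are to the protocol article.

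- **Blinding.** The claim is "Masking is triple and includes participants, outcome assessors, and investigators". The same section then says "Investigator and clinical research assessors will be informed of the rTMS schedule (systematical M-TMS or novel rTMS cure"). One thing alone is kept from them, in the closing words of that sentence: "but not the active or sham nature of the treatment". The nurses who deliver the sessions receive the allocation separately.
- **Study design, setting, and recruitment.** "Arm A with active rTMS cure and systematic maintenance M-rTMS for responders"; "Arm B with a new course of active rTMS at the first sign of depression relapse or recurrence for responders". For arm C: "In this arm, 50% of responders have systematic placebo rTMS maintenance after the cure (arm C1"), and the other half (C2) get a sham course at relapse. Non-responders in every arm go to usual treatment.
- **Randomization.** "Initial randomization is performed according the ratio 1:1:0.5:0.5, respectively, corresponding to arm A, arm B, arm C1" and, last, arm C2.
- **Secondary outcome measures** and the opening of **Statistical analysis.** The secondary criteria are compared for A versus C and B versus C; "only two comparisons will be carried out: arm A versus arm C, and arm B versus arm C". C1 and C2 are pooled.
- **Later in Statistical analysis.** Relapse-free survival and the MADRS, MARS, CRS and CGI scores are instead compared for A versus B and B versus C.

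**The concern.** Concealing active versus sham protects a comparison from rater expectation only when both sides share whatever else the rater knows. Here the rater also knows whether a responder is on regular maintenance or is being watched until mood worsens. An assessor who expects maintained patients to do better, or waiting patients to slip, can carry that into a MADRS or CGI rating.

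Because the known schedule is distributed differently in A, B and pooled C, such an expectation does not cancel. It would push A versus C and B versus C in opposite directions, so one strategy could look better than the other through rating alone. Response and remission are defined on MADRS (Assessments), and sustained MADRS response at 1 year is the criterion on which the trial was sized.

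**Working it through.** **Inputs from the article.** Allocation A:B:C1:C2 = 1:1:0.5:0.5; 318 patients, 106 per arm; initial response of 60% in A and B (Discussion); sustained response of 30% versus 11% (Statistical analysis).

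**Assumed.** Sham response r after the initial course is not given, so r = 10% to 60% is used. The rating shift d is not given and stays a symbol. Loss of 20% is used for illustration.

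**1. The plan's allocation.** 318 × 1/3 = 106 for each of A and B; 318 × 0.5/3 = 53 for each of C1 and C2. The total is 106 + 106 + 53 + 53 = 318, as stated.

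**2. Share allocated to maintenance.** A: 1/1 = 100%. B: 0/1 = 0%. C: 0.5/(0.5 + 0.5) = 50%. Among responders the shares are the same.

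**3. Does the schedule reveal active versus sham?** By allocation, P(active | maintenance) = 1/(1 + 0.5) = 2/3 and P(active | new course) = 1/(1 + 0.5) = 2/3. Among responders, both become 0.6/(0.6 + 0.5r), which is 92% at r = 10% and 67% at r = 60%, but again equal under the two schedules. The schedule adds nothing about active versus sham.

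**4. Shift among responders.** Let d be the rating shift for a patient known to be on maintenance rather than waiting. Bias = d × difference in maintenance share.

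- A versus C: d × (1 - 0.5) = +0.5d
- B versus C: d × (0 - 0.5) = -0.5d
- A versus B: d × (1 - 0) = d
- A versus C1 and B versus C2: 0

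For illustration only, d = 10 percentage points gives +5 and -5 points in the two pooled contrasts.

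**5. Shift across all randomised patients.** If the schedule matters only once delivered, maintenance reaches 0.6 of A, none of B, 0.5r of C and r of C1.

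| r | A v C: (0.6 - 0.5r)d | B v C: -0.5rd | A v C1: (0.6 - r)d |
|---|---|---|---|
| 10% | 0.55d | -0.05d | 0.50d |
| 30% | 0.45d | -0.15d | 0.30d |
| 60% | 0.30d | -0.30d | 0 |

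If the expectation attaches to waiting rather than to maintenance, the sizes for A versus C and B versus C change places.

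**6. Power of the matched contrasts** (30% versus 11%, two-sided 5%). 106 versus 53 gives 79%, or 68% with 20% loss. 106 versus 106 gives 93%, or 87% with 20% loss.

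**The case against.** The strongest reply is that the article limits its masking claim openly to active versus sham, and that this masking works. Splitting arm C between the two schedules ensures that neither schedule points to active treatment. That stands. A reader might infer that telling assessors the schedule unblinds them to active or sham; step 3 shows that it does not. What remains is expectation about maintenance versus waiting, for which the article gives neither size nor direction.

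Other stronger readings also go too far:

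- **All of arm A is on maintenance.** This is true of allocation and of responders only; on the article's 60% response, about 40% of A never starts it.
- **A versus C1 and B versus C2 are free of this bias.** This holds among responders, a subset formed after randomisation. Across all randomised patients, A versus C1 keeps (0.6 - r)d, up to 0.50d in the range shown.
- **Relapse is detected unequally because maintenance patients attend more sessions.** The documents do not show this. Nurses deliver the sessions, one follow-up calendar is listed for all, and attendance is part of the strategy under test.
- **Assessors already know the schedule at the end-of-course MADRS.** The article does not say when they are told.
- **The primary result is biased directly.** It uses EQ-5D and costs; assessor knowledge could reach it only indirectly, for example if a relapse judgement leads to a further course.

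The article also does not say who performs the ratings, and Follow-up has investigators meeting the patients. None of this removes the stated rule that assessors are told the schedule, or its imbalance against pooled C.

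**Conclusion.** The point holds for assessor-rated secondary outcomes: MADRS response and remission, CGI, and relapse judgements so far as they rest on such ratings. The article calls assessors masked while giving them information distributed 100%, 0% and 50% across responders in A, B and C. The resulting shift is about +0.5d in A versus C and -0.5d in B versus C among responders. Across all randomised patients it is about 0.30d to 0.55d in A versus C, given 60% response in A and 10-60% sham response. Whether d is material cannot be settled from the documents.

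In the A versus B comparison written later in Statistical analysis, a responder's schedule is the arm itself, so assessor masking gives no protection there. That passage also conflicts with the two comparisons declared earlier. Active/sham masking is sound.

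**What to change.** 1. **Blinding.** Remove the clinical research assessors from those told the schedule. State that MADRS and CGI raters stay unaware of it and that patients are asked not to mention it. The investigator may still know it.
2. **Statistical analysis.** Add A versus C1 and B versus C2 as sensitivity analyses, keeping pooled C as the main comparator.
3. **Secondary outcome measures and Statistical analysis.** Reconcile A versus C and B versus C with the A versus B and B versus C contrasts given for relapse-free survival and the rating scales.

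The first change does most of the work: step 5 shows that matching alone removes little of the shift when sham response is low.

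**Cost.** A sentence of protocol text, restricted access to the schedule and a sensitivity table from data already collected. Assessors are already named separately from investigators, but where an investigator also rates, rating must pass to the assessor. The matched contrasts have less power (about 79%, or 68% with 20% loss), which is why they should support the pooled analysis and not replace it. No treatment rule changes.
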